## Background

Chordomas (1 - 4% of all malignant bone tumors) of the skull base are relative rare lesions of the bones. The incidence is around 100 new cases per year in Germany and 0.08/100000 in the US corresponding to around 300 new cases per year [1]. Chordomas arise from embryonic remnants of the notochord and are found at the base of the skull area in 35% of all cases. According to the histopathological findings, chordomas are divided into conventional (most common), chondroid and dedifferentiated types [2,3]. Histological differentiation between chordomas and chondrosarcomas is difficult and must contain immunhistochemical tests [4]. Chordoma is immunopositive for epithelial markers like cytokeratin and endothelial membrane antigen (EMA), whereas chondrosarcoma is negative for both. Both chordomas and chondrosarcomas can be positive for S-100 and vimentin.

The average age at the diagnosis is 49 years for base of skull localization. Also, the base of the skull is the most common localisation of chordomas in children and adolescents. In children and adolescents chordomas may behave more aggressively [5]. Men are affected more frequently than women.

Surgical resection is the primary treatment standard, though complete resection is nearly impossible due to close proximity to critical and hence also dose limiting organs for radiation therapy i.e. optic nerves, chiasm and brainstem. Level of recurrence after surgery alone is with reported rates between 50% and 100% [6] comparatively high, so adjuvant radiation therapy is very important for the improvement of local control rates in the primary treatment even after complete resection. Tumour volume is an important prognostic factor, hence a tumour debulking is usually required before radiation therapy application [7]. Other prognostic relevant risk factors are the histological tumour type, resection status, gender, and the age of the patient [8,9].

Radiation resistance is a common characteristic of chordomas [10,11], so high total doses are needed to achive acceptable local control rates after radiotherapy. Conformal precision and image guided radiation therapy techniques provide a safe technique for dose escalation [12]. The physical characteristics of carbon ions or protons such as inverted dose profile allow steep dose gradients and therefore provide further benefit in this field by potentially reducing toxicity.

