### Risk group definition

Secondary objectives of the study will be explorative analysed also according to risk groups mentioned in Table 1.

**Table 1 T1:** Risk group characterization

Low-risk	High-risk
Age > 30 years	Age ≤ 30 years
Male chordoma	Female chordoma
No OAR compression	Compression of OAR
Primary tumour	Recurrent tumor
Tumour size < 70 ml	Tumour size > 70 ml

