### Randomisation

The randomisation will be done using the on-line randomisation tool (Randomizer.at) which is self-serve and runs exclusively on the Internet. An on-screen form with patient details will be completed. The treatment allocation will be immediately notified. The randomisation will be performed regarding treatment arms A and B. Stratification parameters include the following criteria: age (< 30, ≥ 30 years) and gender.

As this is an open-label study there will be no blinding of treatment assignment.

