## Organization, Workflow and Follow-up

Patient data will be collected and documented pseudonymously using electronic data processing (e.g. patient initials, date of birth and study number) at the study office at HIT. Table 3 presents a brief workflow.

**Table 3 T3:** Workflow time table

Approval of ethics committee
↓
Diagnosis of chordoma of the skull base and completion of pre-radiation treatment examinations (biopsy, operation, staging)
↓
Informed consent of the patient and patient registration by the study office at HIT
↓
Stratification and Randomisation
↓
Arm A: carbon ion RT (63 Gy E ± 5%, fractionation 4-6 × 3.0 Gy E) Arm B: proton RT (72 Gy E ± 5%, fractionation 4-6 × 2.0 Gy E)
↓
Treatment planning for particle therapy
↓
Particle therapy
↓
Follow-up

After randomisation the study number will be assigned.

The following study data will be collected at the study office at HIT:

1. Medical reports including pathology reports and results of staging and additional pre-treatment examinations

2. Documentation of RT (dose distributions and DVH) and position checks

3. Prescribed total target dose and fraction doses, treatment interruptions >4 days

4. Toxicity data

5. Follow-up forms

6. Trial-related documentation including severe AE (CTCAE Grad ≥ 3) will be reported immediately to the study office and the principal investigator of the study

7. The date of local recurrence (MRT or CT - morphological tumour progress in the former irradiated region), distant metastases or death of the patient will be reported and documented.

Local recurrences will be confirmed radiologically and histologically whenever possible. At least two medical doctors (radiation oncologist and/or radiologist) will be required to judge of the recurrence or toxicity.

Every patient is followed for LPFS and trial-related AEs for a time period of 8 years. Furthermore, patients will be followed for survival and locoregional recurrences for a time period of 8 years after completion of the irradiation.

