### Efficacy Analysis

#### Primary efficacy analysis

LPFS is defined as the time from date of randomisation to local recurrence or death from any cause in the absence of documented local disease progression. LPFS will be censored on the date of the last tumour assessment on study for patients who do not have local tumour progression and who do not die while on study.

A log-rank test (two-sided) will be used to compare LPFS between the two treatments. The LPFS-rates will be derived from the Kaplan Meier estimate [22] and the confidence intervals will be calculated using Greenwood's formula.

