#### Secondary efficacy analyses

A sensitivity analysis will be performed on the primary efficacy endpoint to assess the impact of protocol deviations using the per protocol analysis set.

A hazard ratio with 95% confidence interval for the experimental arm relative to control arm will be estimated by proportional hazard regression [23-25] with treatment, gender, age (< 30, ≥ 30 years), tumour size (< 70 ml, ≥ 70 ml), compression of OAR (yes/no) as covariates. A logistic regression analysis [26] will be carried out to identify relevant prognostic factors. Benefit from intervention (yes or no) will be defined as belonging to the patients groups (low-risk, high-risk group) which lay above the 50% percentile of LPFS.

The analyses of OS, PFS and metastasis free survival will be conducted using log-rank test. The Kaplan-Meier method will be used to obtain the estimates of the survival functions and the 95% confidence intervals will be estimated using Greenwood's formula. Covariates will not be included in the calculation.

All of these secondary analyses will be conducted at the 0.05 level of significance.

Descriptive statistics will be provided for all other secondary endpoints. Additional exploratory analyses will be used as appropriate. Generally, results will be given by summaries of the data as indicated above together with the test statistics and their associated p-values. Appropriate confidence intervals of estimates of effect will be given to quantify the degree of uncertainty of the point estimates.

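### The secondary Cox model leaves out primary versus recurrent tumour, histological type and resection status, although the protocol itself treats all three as prognostic (minor)

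*Protocol article*

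**What the plan says.** **The model.** Secondary efficacy analyses in the protocol article estimates the treatment hazard ratio by proportional hazards regression on treatment, gender, age (split at 30 years), and "tumour size (< 70 ml, ≥ 70 ml), compression of OAR (yes/no) as covariates". Variables and cut-points are named, so the list is closed. The primary analysis supplies no hazard ratio: "A log-rank test (two-sided) will be used to compare LPFS between the two treatments", accompanied by Kaplan-Meier rates. A hazard ratio is also mentioned for the interim analysis, but for the final analysis this Cox model is the only source specified.

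**The factors the protocol regards as prognostic.** The Background singles out tumour volume and then adds: "Other prognostic relevant risk factors are the histological tumour type, resection status, gender, and the age of the patient". Table 1 in Risk group definition uses five factors: age, gender, OAR compression, tumour size, and primary against "Recurrent tumor" status. Of their use it says: "Secondary objectives of the study will be explorative analysed also according to risk groups mentioned in Table 1".

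**Balance and data.** Under Randomisation: "Stratification parameters include the following criteria: age (< 30, ≥ 30 years) and gender". Under Organization, Workflow and Follow-up, the study office collects "Medical reports including pathology reports and results of staging and additional pre-treatment examinations".

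**The concern.** A pre-specified covariate list should be consistent with what the same document says drives outcome. Here four of the five Table 1 factors are in the model and the fifth is not; two further factors named as prognostic in the Background are also absent. No reason is given.

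All three can vary in this trial. Eligibility excludes prior radiotherapy to the skull base but not recurrent tumours, and it restricts neither histological subtype nor extent of resection. Stratification does not balance any of the three.

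At stake is the reported effect size, on the scale used to design the trial. In a Cox model with a real treatment effect, omitting prognostic factors moves the treatment hazard ratio towards 1 relative to the ratio conditional on them, even under perfect randomisation. The adjusted test loses power, and chance imbalance on those factors stays uncorrected in the estimate.

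**Working it through.** **1. Covariates side by side**

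| Factor | Background | Table 1 | Cox model | Stratified |
|---|---|---|---|---|
| Gender | yes | yes | yes | yes |
| Age | yes | yes | yes | yes |
| Tumour size/volume | yes | yes | yes | no |
| OAR compression | no | yes | yes | no |
| Primary vs recurrent | no | yes | **no** | no |
| Histological type | yes | no | **no** | no |
| Resection status | yes | no | **no** | no |

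**2. The plan's own figures (Sample Size Determination)**

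- Hazards: −ln(0.70)/5 = 0.0713 and −ln(0.80)/5 = 0.0446. The unrounded ratio is 1.598, or 0.626 for carbon against proton.
- Schoenfeld events: 4(1.960 + 0.842)²/(ln 1.598)² = 142.7, so 143.
- Event probability with uniform 5-year accrual and a 13-year maximum: 1 − [exp(−8λ) − exp(−13λ)]/(5λ) = 0.525 and 0.373, mean 0.449. Patients: 143/0.4487 = 318.7, so 319.
- With 7% loss: 319/0.93 = 343.01, so 344.

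All figures reproduce, and none depends on the Cox covariates.

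**3. Effect of leaving the factors out**

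The documents give neither prevalence nor effect size for any of the three, so these are assumptions: three independent binary factors, prevalence 30% each, with the same hazard ratio of 1.5, 2 or 3. Simulation: 1,500 trials per scenario, 344 patients allocated 1:1, control 5-year LPFS 70%, conditional treatment HR 0.626, accrual and follow-up as planned, 7% random loss. Each data set was fitted without and with the three factors. The covariates already planned were not simulated.

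| Factor HR | Treatment HR, without / with | SE of log HR, without / with | Power, without / with |
|---|---|---|---|
| 1 (no effect) | 0.627 / 0.625 | 0.1668 / 0.1677 | 0.818 / 0.813 |
| 1.5 | 0.628 / 0.618 | 0.1677 / 0.1689 | 0.795 / 0.811 |
| 2 | 0.650 / 0.621 | 0.1687 / 0.1703 | 0.729 / 0.813 |
| 3 | 0.680 / 0.618 | 0.1720 / 0.1744 | 0.625 / 0.787 |

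The comparison to read is within a row, because both models use the same simulated trials.

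- Shift in log HR: ln(0.628/0.618) = 0.016, ln(0.650/0.621) = 0.046, ln(0.680/0.618) = 0.096, against an SE of about 0.17.
- Power lost by omission: 1.6, 8.4 and 16.2 points.
- Change in SE on adding the factors: 0.1689/0.1677, 0.1703/0.1687 and 0.1744/0.1720 give rises of 0.7%, 0.9% and 1.4%.
- With no treatment effect (factors at HR 2): HR 0.998 / 1.001, rejection rate 0.060 / 0.058. There is no attenuation and no change in type I error.

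A second simulation used 320 patients, recurrent tumour in 30% (HR about 1.8–2.0) and subtotal resection in 40% (HR 1.5), added to a model that already had treatment and tumour volume. The mean HR moved from 0.635–0.641 to 0.623–0.630. Power rose from 0.749, 0.763, 0.779 and 0.781 to 0.788, 0.799, 0.807 and 0.797, that is by 1.6 to 3.9 points. Histology was not simulated there.

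**4. Chance imbalance**

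For one factor at an assumed 30% prevalence with 172 patients per arm, the SD of the between-arm difference is √(0.3 × 0.7 × 2/172) = 0.049. A gap of 5 points or more (z = 1.01) has a probability of about 31%, and one of 10 points or more (z = 2.02) about 4%. With a factor HR of 2, prevalences of 35% and 25% give an early hazard ratio between arms of 1.35/1.25 = 1.08 from imbalance alone.

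**The case against.** The best defence is that a short pre-specified list is legitimate and that this one is reasonable: both stratification factors, four of five Table 1 factors, and tumour volume. The Background suggests sparse categories too, since complete resection is described as nearly unattainable and the conventional subtype as the commonest. Randomisation already allows for chance imbalance in the test and interval. The model with fewer covariates estimates a different hazard ratio, not a confounded one. All of this stands and keeps the point small, but it does not explain why one Table 1 factor was singled out for omission.

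A reader might infer more than the documents support:

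- **Precision is lost.** It is not. The standard error of the log HR is slightly smaller without the factors. The loss is in power, through attenuation.
- **The prognostic-factor objective cannot be met.** The same section plans a logistic regression for prognostic factors, without a restricted candidate list, and risk-group analyses by Table 1 include recurrent status.
- **All three items are already collected.** Recurrent status is needed for Table 1, and histology is in the pathology reports. Resection status is not a named data item. It is only implied by the medical reports and by the surgical reports used for target definition.
- **It is merely left to the statistical analysis plan.** Analysis details are deferred in general, but this covariate list is fixed in the protocol article itself.

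**Conclusion.** The inconsistency is real and minor. The secondary Cox model omits one of the protocol's own five risk factors and two further factors it calls prognostic, without a reason, and it is the only specified source of the final treatment hazard ratio and its interval.

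Under the stated assumptions, the cost is about 0.01 on the HR scale and 2 points of power for three factors with HR 1.5, and about 0.03 and 8 points for HR 2. HR 3 for all three is an extreme case. These sizes rest on independent factors at 30% prevalence and on leaving the planned covariates out of the simulation. If the omitted factors overlap with tumour size or OAR compression, the gain over the planned model would be smaller. Recurrent status alone was not simulated and would account for only part of it.

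It would be wrong to infer that the trial's main conclusion is at risk. The primary test is an unadjusted log-rank test. The 143 events, 319 and 344 patients and the type I error do not change, and nothing is attenuated if the treatments are equivalent.

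**What to change.** Before outcome data by arm have been looked at, add primary versus recurrent tumour to the Cox covariates in Secondary efficacy analyses. Add histological type (rare categories pooled) and resection status where they can be coded from the collected pathology and medical reports; where they cannot, state why they are left out. Fixing this in advance matters because the trial is open-label and a later choice of covariates would invite criticism.

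Cost: a change of wording and the coding of up to three baseline items. The model grows from 5 parameters (143/5 = 28.6 events each) to 8 or 9 (143/8 = 17.9; 143/9 = 15.9), and the standard error of the log HR rises by about 1% (0.7% to 1.4% in the scenarios above). The log-rank test and sample size need no change.

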### Secondary objectives of the study

1. Assessment of overall survival, progression free and metastasis free survival, patterns of recurrence, local control rate and morbidity.

2. Prognostic factors, definition of patients who will benefit from the adjuvant therapy, risk group definition.

3. Plan quality (target coverage, sparing of organs at risk, integral dose).

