### Sample Size Determination

The sample size is calculated on the basis of the following assumptions:

• LPFS rate 5 years after radiation therapy of 70% 1) for proton therapy, hazard λ_1 _= 0.0713, and 80% for carbon ion therapy, hazard λ_2 _= 0.0446 (hazard ratio = 1.599).

• Recruitment period of 5 years, with constant accrual rate of 20% patients per year and a follow-up time of 8 years.

• One interim analysis according to a group sequential design with two stages.

Formula of Schoenfeld [20,21] used for the calculation of the number of accumulated events. For a two-sided logrank test with an overall two-sided significance level of 0.05 (including interim and final analyses) and power of 0.80, 143 events are required. The critical values and the test characteristics of the group sequential test design were calculated for an O'Brien and Fleming type alpha spending function. The computation assumes equal allocation to the two groups (n_2_/n_1 _= 1). Assuming an accrual time of 5 and a maximum observation time of 13 years a total of 319 patients is expected to yield the necessary number of events if the accrual rate is constant. Under these assumptions, the time point of the interim analysis should be 7 years after the first patient is entered. The ADDPLAN, Version 4.0 calculator was used for the sample size estimation. With the assumption that approximately 7% of the patients will be lost to follow-up a total of 344 patients will be needed to accumulate 143 events.

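### The rule that labels patients as benefiting compares no treatments, so it measures prognosis, and its median cut-off is fragile

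*Protocol article*

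**What the plan says.** All references are to the protocol article.

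- **Objective.** Secondary objectives of the study, item 2: "Prognostic factors, definition of patients who will benefit from the adjuvant therapy, risk group definition".
- **Analysis.** Secondary efficacy analyses: "A logistic regression analysis [26] will be carried out to identify relevant prognostic factors". The next sentence, which concerns LPFS, reads "Benefit from intervention (yes or no) will be defined as belonging to the patients groups (low-risk, high-risk group) which lay above the 50% percentile". The same section plans a Cox model with treatment, gender, age, tumour size and compression of organs at risk as covariates. It lists no interaction with treatment.
- **Status.** Risk group definition: "Secondary objectives of the study will be explorative analysed also according to risk groups mentioned in Table 1". Secondary efficacy analyses nevertheless places its analyses at the 0.05 level.
- **Assumed rates.** Sample Size Determination: "LPFS rate 5 years after radiation therapy of 70"% for protons "and 80% for carbon ion therapy".
- **Follow-up.** Organization, Workflow and Follow-up gives each patient 8 years of follow-up for LPFS. Sample Size Determination uses 5 years of accrual and up to 13 years of observation.
- **Cut-offs.** Table 1 puts age 30 and under in the high-risk column and separates tumour size into under 70 ml and over 70 ml. Randomisation stratifies by "age (< 30, ≥ 30 years) and gender". The Cox model uses the same age split and puts exactly 70 ml in the upper class.

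**The concern.** Benefit is a contrast: the outcome on one treatment set against the outcome the same kind of patient would have had on the other. The rule contains no such contrast. It asks only whether a risk group's LPFS is high, and a group can have high LPFS because its disease is less aggressive, whichever beam it receives. No other stated analysis fills the gap, because the Cox model as listed estimates one treatment hazard ratio common to all risk groups.

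The part of secondary objective 2 that asks who benefits would then be answered with a statement about prognosis. A reader of the trial report could take it as evidence for selecting patients for treatment, although no difference in treatment effect had been examined.

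Two further weaknesses concern how the rule would operate: the 50% point of LPFS lies late on the plan's own assumptions, and a yes/no outcome cut from LPFS does not accommodate censoring.

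**Working it through.** **1. The plan's own figures.** Inputs from Sample Size Determination: 5-year LPFS 70% and 80%, two-sided 0.05, power 0.80, 1:1 allocation, 5 years of accrual, 13 years in total, 7% loss.

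- Hazards: −ln(0.70)/5 = 0.0713 and −ln(0.80)/5 = 0.0446 per year; ratio 1.598 (the plan gives 1.599).
- Schoenfeld events: 4 × (1.960 + 0.842)² / (ln 1.598)² = 142.7, so 143.
- Event probability with 8 to 13 years of follow-up: 1 − [exp(−8λ) − exp(−13λ)]/(5λ) = 0.525 for protons and 0.373 for carbon ions; mean 0.449. 143/0.449 gives 319 patients, and 319/0.93 gives 344.

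The plan's figures reproduce, so its hazards can be used below.

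**2. What the label would track.** The documents give no LPFS by risk group, so this step rests on assumptions: two risk groups of equal size, proton 5-year LPFS averaging 70%, and a between-group hazard ratio g of 1.5, 2 or 3. Solve [exp(−5h) + exp(−5gh)]/2 = 0.70 for the low-risk hazard h. With no treatment effect, the medians are ln 2/h and ln 2/(gh). With the design treatment effect the same in both groups, the 5-year gain is exp(−5h/1.598) − exp(−5h), and likewise with gh in place of h.

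| g | Median LPFS, no treatment effect: low / high risk (years) | 5-year gain, same treatment hazard ratio: low / high risk (points) |
|---|---|---|
| 1.5 | 12.1 / 8.0 | 8.5 / 11.4 |
| 2 | 14.3 / 7.1 | 7.5 / 12.3 |
| 3 | 18.5 / 6.2 | 6.0 / 13.3 |

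The middle column shows the better-prognosis group ranking first when neither treatment is better. The last column shows that, with one common hazard ratio, the larger absolute gain falls in the other group. The label can therefore point away from the patients who gain most on that scale.

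**3. Where the 50% point lies.** Median = ln 2/λ: 0.693/0.0713 = 9.7 years (protons) and 0.693/0.0446 = 15.5 years (carbon ions). Solving 0.5 exp(−0.0713t) + 0.5 exp(−0.0446t) = 0.5 gives a pooled median of 12.2 years. The chance that the Kaplan-Meier curve reaches 50% comes from 4,000 simulated trials with 160 patients per arm and no losses.

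| Follow-up reading | Quantity | Protons | Carbon ions | Pooled |
|---|---|---|---|---|
| 8 years per patient | LPFS at 8 years | 56.5% | 70.0% | 63.2% |
| 8 years per patient | Chance median reached | about 4% | 0% | 0% |
| 8 to 13 years | LPFS at 13 years | 39.6% | 56.0% | 47.8% |
| 8 to 13 years | Chance median reached | about 97% | about 13% | about 66% |

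On the second reading, the fraction of patients with follow-up as long as the pooled median is (13 − 12.18)/5 = 0.164. The number at risk there is 160 × 0.164 × (0.419 + 0.581), about 26 of 320.

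A single risk group reaches its own median by 8 years only if its 5-year LPFS is at most 0.5^(5/8) = 65%, and by 13 years only if it is at most 0.5^(5/13) = 77%.

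**4. The logistic model.** Analysis Populations and General Considerations censors incomplete follow-up at the last follow-up date and imputes nothing. If the outcome is LPFS beyond a cut, a patient censored before the cut has neither yes nor no. If the outcome is instead the label attached to a whole risk group, it is fixed by the Table 1 factors, and regressing it on those factors is circular.

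**5. Cut-offs.** A patient aged exactly 30 is high-risk in Table 1 but in the older class for stratification and the Cox model. Exactly 70 ml has no column in Table 1 but is in the upper class of the Cox model.

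**The case against.** The strongest reply is that this is a secondary analysis described as exploratory, that an adjusted Cox model is already planned, and that details are left to an analysis plan that is not shown. The first two points limit the severity. The third does not remove the point: the article does not leave the definition open but fixes one, and an analysis plan that followed it would inherit the fault. The 0.05 level set for the secondary analyses also sits uneasily with the exploratory description.

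Four stronger readings are tempting, and the documents do not support them:

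- **The trial cannot reach the median.** That holds for 8 years of follow-up per patient. Under the 13-year maximum on which the sample size rests, the proton median is very likely reached and the pooled median more often than not. The rule also concerns risk groups, and a poor-prognosis group could reach its median sooner. The 50% point might moreover mean a Kaplan-Meier median, a 50% LPFS rate or the median of observed times; the last always exists but ignores censoring.
- **The low-risk group is labelled as benefiting by construction.** Table 1 lists single factors with no rule for combining them, and the data decide which group lies above the cut. A tendency is all that can be claimed.
- **The label means benefit from carbon ions.** The text speaks of the intervention and, in the objective, of adjuvant therapy, which both arms receive. The defect remains on the broader reading, because no arm is untreated.
- **The label is the outcome of the logistic model.** The adjacent sentences suggest this but do not say it. The stated purpose of that model is to find prognostic factors.

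**Conclusion.** The point holds in limited form. The definition contains no between-arm comparison, so it describes prognosis and cannot answer who benefits. This follows from the wording alone and needs no numerical assumption. The direction of the likely mislabelling does rest on the assumed risk groups: with no treatment effect, the low-risk median exceeds the high-risk one by 4.1 years (12.1 − 8.0) at g = 1.5 and by 12.3 years (18.5 − 6.2) at g = 3.

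The cut-off is fragile rather than impossible. Its availability depends on which follow-up statement applies, on exponential LPFS at the plan's hazards, and on reading the 50% point as a Kaplan-Meier median. The censoring objection is conditional on the logistic outcome being cut from LPFS. The mismatches at age 30 and at 70 ml are real but minor.

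The change should be made, but it concerns a secondary, exploratory question. The primary log-rank comparison of LPFS is untouched.

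**What to change.** 1. Delete the definition of benefit. In its place, add treatment-by-risk-group interaction terms to the planned Cox model, and report the carbon/proton hazard ratio with 95% CI within each risk group, labelled exploratory.
2. Identify prognostic factors from that Cox model, which handles censoring, instead of logistic regression.
3. Use one set of analysis cut-offs in Table 1, stratification and models, so that age exactly 30 and size exactly 70 ml each fall in one class throughout. State whether a risk group is a single Table 1 row or a combination. Primary versus recurrent tumour is in Table 1 but not among the Cox covariates, and would have to be added if that row is examined.
4. Reconcile the 8-year and 13-year statements on LPFS follow-up, since any late LPFS estimate depends on them.

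The cost is wording only, with no extra patients or data. The price is imprecision. The design is sized for the overall comparison ("including interim and final analyses) and power of 0.80, 143 events are required"). If those events split evenly over two risk groups and two arms (an assumption), the standard error of a within-group log hazard ratio is about 2/√71.5 = 0.237, so its 95% CI runs from the estimate divided by exp(1.96 × 0.237) = 1.59 to the estimate times 1.59. For the interaction, the standard error is about 4/√143 = 0.334 and the factor is exp(1.96 × 0.334) = 1.93. Such estimates can describe but not settle who benefits, and the report should say so.
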